## Abstract

**Abstract:**

**Introduction:**

Knowledge about the late effects of COVID-19, or so-called post-acute sequelae of COVID (PASC), and its pathogenesis is still very limited. The purpose of this observational study is to chart late neurocognitive effects of the COVID-19 infection. The aim is to increase knowledge of the underlying biological processes and describe how biomarkers correlate with degree of symptoms, mapping their role as diagnostic markers over time (24 months).

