**Methods and analysis:**

This prospective observational cohort study is longitudinal and monitors patients with neurocognitive and psychological symptoms after COVID-19 infection in order to analyse the impact on the brain. For these purposes, we introduce a digital neuropsychological platform (Mindmore). We also aim to analyse potential diagnostic and prognostic markers from blood and cerebrospinal fluid and use MRI of the brain. We will measure the patients’ return to work and studies as well as any impact on their ADL functions and quality of life. The ongoing study aims to follow-up to 100 study participants with PASC for 24 months at three visits: baseline, 12 months and 24 months. The findings of the study can be used as guidance for future policy management in healthcare and may lead to a possible curative or symptom-relieving treatment.

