**Trial registration number:**

NCT06298006.

STRENGTHS AND LIMITATIONS OF THIS STUDYA study population that reflects the population of a well-defined, demographically diverse area in Sweden.Large amount/number of analysed biomarkers, including biomarkers from cerebrospinal fluid, that are difficult to obtain and therefore rarely investigated.Long follow-up period, 24 months.No control group built into the study design, but normative data for neurocognitive testing are available and will be used.Relatively low number of participants, which can possibly make statistical analysis of subgroups difficult.

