PASC is hitherto neither fully characterised nor understood, making it a challenging condition to provide adequate medical management but which impacts seriously the activities of daily living (ADL) in those affected.^8^ PASC may lead to lengthy and recurrent periods of sick leave, costly for both the individual and for society at large.^13^ Subramanian *et al* report that PASC is associated with gender, ethnicity, socioeconomic status and a comorbidity burden.^14^ Since many related symptoms are self-reported, this imposes particular demands on the clinician to objectify findings. In a Swedish study, Wahlgren *et al* describe that cognitive impairment, sensorimotor symptoms and fatigue were the most prevalent even after 24 months follow-up with no difference between hospitalised and non-hospitalised patients.^15^ Cognitive symptoms have been further confirmed in a large community sample, irrespective of COVID-19’s duration.^16^ Furthermore, in a subgroup, white matter lesions were a common finding in MRI scans, which is also confirmed in other radiology studies.^15 17 18^

At present, there is an urgent need for objective biomarkers to assess and independently differentiate symptoms related to PASC from other morbidities in order to establish and provide appropriate rehabilitation alternatives. Increasingly, studies indicate immune activation that occurs during a moderately severe to severe COVID-19 infection and is similar to the one seen after hypoxic brain injury.^3 19^ This activation can be correlated with levels of cytokines and, for example, neurofilament light (NfL). NfL is an intermediate filament important for maintaining axonal stability and growth.^20^ Axonal damage results in the leakage of NfL into the cerebrospinal fluid (CSF), making it a marker for ongoing neuroaxonal degeneration. Another genetic biomarker: ApoE e4 genotype, long known to be associated with Alzheimer’s disease, has also been linked to the increased risk of developing a more serious COVID-19 infection, independent of pre-existing dementia, cardiovascular disease and type 2 diabetes.^21^

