Certified sick-leave	Asthma/COPD/cancer/diabetes/heart insufficiency/hypertension/orthostatism/ hypercholesterolaemia/ neurological disorder/hypothyroidism/other
COVID-19 symptoms	Organ/specific symptoms
Smell/taste dysfunction	Remaining symptoms/previously

The *inclusion criteria* include COVID-19 infection confirmed by positive laboratory test (PCR test for SARS-CoV-2) taken during the acute infection, residual neurocognitive symptoms more than 3 months after the initial COVID-19 infection and an age of more than 18 years. Full-spectrum COVID severity cases will be included.

The *exclusion criteria* are severe cancer, dementia and ongoing alcohol or drug abuse. Included participants will then undergo baseline evaluation (figure 1). First when patients are included and have signed the patient consent form, they will then be tested using the neuropsychological tests tested via the digital platform Mindmore AB (www.mindmore.com).^23^ Mindmore is CE marked, approved, and purchased by the Research Centre of Region Örebro County. Trial participants may withdraw from the study at any time. Patients will receive no monetary compensation for study participation.

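### The abstract gives biomarkers a diagnostic aim, but only PASC patients are enrolled, so diagnostic accuracy for PASC cannot be estimated

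*Protocol article*

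**What the plan says.** All references are to the protocol article.

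- **Aim.** The Introduction of the abstract says the study will "describe how biomarkers correlate with degree of symptoms, mapping their role as diagnostic markers over time". The abstract's Methods and analysis paragraph adds: "We also aim to analyse potential diagnostic and prognostic markers from blood and cerebrospinal fluid and use MRI of the brain".
- **Population.** The same paragraph says: "The ongoing study aims to follow-up to 100 study participants with PASC for 24 months at three visits". The inclusion criteria (Study population) require laboratory-confirmed infection and "residual neurocognitive symptoms more than 3 months after the initial COVID-19 infection".
- **Comparator.** The strengths and limitations list says: "No control group built into the study design, but normative data for neurocognitive testing are available and will be used". Variables studied confirms that these norms turn raw cognitive test results into z-scores.
- **Markers.** Blood, CSF and faecal samples are taken at baseline and 24 months, and MRI at inclusion and at the end of the study (Variables studied, Table 2). No group without PASC is named for any of them.
- **Analysis.** Statistical analysis provides for comparisons between independent groups but defines no non-PASC group.

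**The concern.** A diagnostic marker for PASC has to separate people who have it from people who do not, such as those who recovered fully from COVID-19 or who have similar symptoms from another cause. This cohort contains only the first kind. The one mitigation offered, normative data, applies to the cognitive tests and does not reach the biomarkers that the diagnostic aim is about.

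The abstract's Introduction places the diagnostic role next to correlation with degree of symptoms, as if the second could establish the first. It cannot. What is at stake is the label on the results: severity associations from this cohort, including those from repeated lumbar puncture, could be published as diagnostic findings that the design does not support.

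**Working it through.** The article states no sensitivity, specificity, AUC or power, so there is no figure to reproduce. The check is whether the diagnostic quantities exist under this design.

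**Inputs from the article**
- PASC participants: about 50 to 100 (Sample size calculation).
- Non-PASC participants, n0: 0 (inclusion criteria; strengths and limitations).
- Attrition in a similar study: up to 40% (Discussion).
- Significance level: 0.05 (Statistical analysis). Two-sided testing and 80% power are my assumptions.

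**1. Diagnostic quantities**
- Specificity = TN / (TN + FP). The denominator is n0 = 0, so it is undefined.
- Positive likelihood ratio = sensitivity / (1 − specificity), and negative likelihood ratio = (1 − sensitivity) / specificity. Both are undefined.
- AUC is the probability that a random case exceeds a random non-case. It needs n0 > 0, so it is undefined.
- Sensitivity uses cases only, but needs a cut-off from elsewhere and says nothing about discrimination by itself.

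None of this depends on the number of cases. The problem is identification, not precision.

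**2. Correlation among cases is a different quantity**
- A marker raised equally in every case could separate cases from non-cases well, yet have zero correlation with severity.
- A marker that follows depressive symptoms could correlate with symptom burden and have no specificity for PASC. The Discussion supplies a candidate: it notes that kynurenic acid rises in major depression, and kynurenic acid is on the study panel.

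**3. What the cohort can answer**

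Smallest correlation detectable (Fisher z): r = tanh[(1.960 + 0.842) / √(n − 3)].

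| n | Basis | r |
|---|---|---|
| 100 | upper end | tanh(2.802/√97) = 0.28 |
| 60 | 100 less 40% | tanh(2.802/√57) = 0.36 |
| 50 | lower end | tanh(2.802/√47) = 0.39 |
| 30 | 50 less 40% | tanh(2.802/√27) = 0.49 |

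These are for one correlation at a time, without allowance for multiple markers. Moderate severity associations are within reach.

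**4. What a comparator would change (assumed figures only)**

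With n0 = 50 and an observed specificity of 0.80, the Wilson 95% interval has centre (0.80 + 3.84/100) / (1 + 3.84/50) = 0.779 and half-width 1.96 × √(0.80 × 0.20/50 + 3.84/10000) / (1 + 3.84/50) = 0.109, giving 0.67 to 0.89. With n0 = 100 the interval is 0.71 to 0.87. The quantity becomes estimable, though imprecisely, only once non-cases exist.

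**The case against.** The authors list the missing control group as a limitation, call the study exploratory and, in the abstract's methods, speak only of potential markers. They promise no cut-off, specificity or validated test. The aim that closes the Background speaks of exploring correlations and makes no diagnostic claim. All of this stands, and it means nothing is concealed. It does not make the quantity estimable: exploratory work may be imprecise, but here the denominator is empty. The methods paragraph also names diagnostic and prognostic markers as two things, so the first is hard to read as loose wording for the second. An unseen analysis plan cannot supply non-cases either.

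Four stronger readings are tempting and are not supported:

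- **That the Background sets PASC versus other morbidities as a study aim.** The sentence on "objective biomarkers to assess and independently differentiate symptoms related to PASC from other morbidities" describes a need in the field. The point rests on the abstract, not on that sentence.
- **That true diagnostic markers would be discarded.** Statistical analysis contains no rule for dropping markers. Depression, stress and PTSD symptoms are measured, so overlap with them can at least be examined.
- **That the cohort offers no useful contrast.** Participants are cases at inclusion, not necessarily at 24 months. Persistent versus resolved symptoms, change within a person, and scores above versus below the Mental Fatigue Scale cut-off of 10.5 can all be studied. These concern prognosis or severity. Laboratory reference limits could also be set beside the results, but they would not represent people with similar symptoms from other causes.
- **That a range of predictive values can be computed.** The article gives no marker sensitivity. Its 10–30% is the occurrence of PASC among non-hospitalised COVID-19 patients, not its prevalence among referred, symptomatic people who would be tested.

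**Conclusion.** The point holds as a mismatch between stated aim and design. With n0 = 0, specificity, likelihood ratios and AUC for PASC versus non-PASC cannot be estimated for any blood, CSF, faecal or MRI marker, at any sample size in the planned range. The planned correlation with degree of symptoms answers a question about severity.

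The severity and prognostic aims are not affected, and the study is not invalid. This conclusion rests only on the article's own account of its participants and its missing control group. The detectable correlations rest in addition on the assumed 80% power and two-sided test. The change should be made because it governs what the study may conclude.

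**What to change.** - In the abstract's Introduction and its Methods and analysis paragraph, replace *diagnostic* with wording such as: *associated with symptom severity, and prognostic for 12- and 24-month outcome (including persistent versus resolved symptoms)*.
- State that no conclusion on diagnostic accuracy for PASC will be drawn from this cohort.
- Label any comparison of biomarkers with laboratory reference limits as descriptive.

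The cost is a few lines of text and a less ambitious claim. No new participants, samples or visits are needed. Keeping a diagnostic aim would instead require a comparator group measured with the same assays, which is a much larger change for a study already recruiting and is not needed to resolve this point.

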**Methods and analysis:**

This prospective observational cohort study is longitudinal and monitors patients with neurocognitive and psychological symptoms after COVID-19 infection in order to analyse the impact on the brain. For these purposes, we introduce a digital neuropsychological platform (Mindmore). We also aim to analyse potential diagnostic and prognostic markers from blood and cerebrospinal fluid and use MRI of the brain. We will measure the patients’ return to work and studies as well as any impact on their ADL functions and quality of life. The ongoing study aims to follow-up to 100 study participants with PASC for 24 months at three visits: baseline, 12 months and 24 months. The findings of the study can be used as guidance for future policy management in healthcare and may lead to a possible curative or symptom-relieving treatment.

**Ethics and dissemination:**

This study was approved by the Swedish Ethical Review Authority (diary number: 2020–0604 (main application), 2021–03205, 2023–00023-02, 2024–00426-02 (amendments)). Participants will be required to provide informed consent. The results of this study will be reported in peer-reviewed journals and presented at scientific conferences.

**Trial registration number:**

NCT06298006.

STRENGTHS AND LIMITATIONS OF THIS STUDYA study population that reflects the population of a well-defined, demographically diverse area in Sweden.Large amount/number of analysed biomarkers, including biomarkers from cerebrospinal fluid, that are difficult to obtain and therefore rarely investigated.Long follow-up period, 24 months.No control group built into the study design, but normative data for neurocognitive testing are available and will be used.Relatively low number of participants, which can possibly make statistical analysis of subgroups difficult.

## Background

 The WHO reports that since the outbreak of Severe Acute Respiratory Coronavirus 2 (SARS-CoV-2) in China in December 2019, over 778 million individuals have been infected, and over 7 million (7 098 155 as of 21–07-2025) deaths are confirmed associated with coronavirus disease 2019 (COVID-19).^1^ Before the initialisation of widespread vaccination programmes, many patients had severe respiratory difficulties and were in need of hospitalisation.^2^ However, the majority of patients have mild symptoms of SARS-CoV-2 including fever, coughs and fatigue, but most are, however, asymptomatic.^3^ Other commonly reported acute symptoms include sore throats, headaches, conjunctivitis and medical issues concerning the gastrointestinal tract.^4^ It has been noted that a number of patients have prolonged or, indeed, persistent symptoms including dyspnoea, fatigue, postexertional malaise and cognitive impairment requiring reduced working hours in almost half and inability to work in 22% of patients.^5 6^ Studies have shown that a significant proportion of patients who have a history of COVID-19 infection might show *neurological symptoms* such as headache, fatigue, epileptic seizures, impaired consciousness and ataxia; *psychiatric conditions* such as depression and anxiety and PTSD symptoms as well as *cognitive* impairment.^6 7^ Thus far, over 200 symptoms related to post-COVID-19 syndrome have been reported and affect almost all human physiological systems.^7 8^ The number of individuals reporting continued symptoms beyond 12 weeks is not insignificant and has led the National Institute for Health and Care Excellence (NICE) to term the condition ‘post-Covid-19 syndrome’ (PCC),^9^ while the term ‘long-covid’ (LC) is also widely used in research.^10^ Post-acute sequelae of COVID (PASC) occur in an estimated 10–30% of non-hospitalised patients and about twice as often in those who were hospitalised.^11^ In early phases of the pandemic, Hedberg *et al* reported a 4.8% hospitalisation rate among individuals testing positive for COVID-19 in Stockholm.^12^ Even with cautious estimations, it is approximated that worldwide as many as 65 million people may suffer from long-term symptoms from COVID-19 and cases are predicted to increase.^10 11^

PASC is hitherto neither fully characterised nor understood, making it a challenging condition to provide adequate medical management but which impacts seriously the activities of daily living (ADL) in those affected.^8^ PASC may lead to lengthy and recurrent periods of sick leave, costly for both the individual and for society at large.^13^ Subramanian *et al* report that PASC is associated with gender, ethnicity, socioeconomic status and a comorbidity burden.^14^ Since many related symptoms are self-reported, this imposes particular demands on the clinician to objectify findings. In a Swedish study, Wahlgren *et al* describe that cognitive impairment, sensorimotor symptoms and fatigue were the most prevalent even after 24 months follow-up with no difference between hospitalised and non-hospitalised patients.^15^ Cognitive symptoms have been further confirmed in a large community sample, irrespective of COVID-19’s duration.^16^ Furthermore, in a subgroup, white matter lesions were a common finding in MRI scans, which is also confirmed in other radiology studies.^15 17 18^

At present, there is an urgent need for objective biomarkers to assess and independently differentiate symptoms related to PASC from other morbidities in order to establish and provide appropriate rehabilitation alternatives. Increasingly, studies indicate immune activation that occurs during a moderately severe to severe COVID-19 infection and is similar to the one seen after hypoxic brain injury.^3 19^ This activation can be correlated with levels of cytokines and, for example, neurofilament light (NfL). NfL is an intermediate filament important for maintaining axonal stability and growth.^20^ Axonal damage results in the leakage of NfL into the cerebrospinal fluid (CSF), making it a marker for ongoing neuroaxonal degeneration. Another genetic biomarker: ApoE e4 genotype, long known to be associated with Alzheimer’s disease, has also been linked to the increased risk of developing a more serious COVID-19 infection, independent of pre-existing dementia, cardiovascular disease and type 2 diabetes.^21^

Another area of increasing clinical interest is gut bacterial microbiome in COVID-19, which is described as having decreased diversity and richness and persistent bacterial microbiome dysbiosis even after disease resolution.^22^ The gut mycobiome in COVID-19 is characterised by increased faecal fungal load and increased beta-diversity (more heterogeneous), and it is unstable over time and persistently altered after disease resolution. With this in mind, the present prospective study aims to collect clinically significant demographic, medical, neurocognitive data in patients with documented COVID-19 infection and to explore correlations between inflammation, neurocognitive findings, and the impact on the individual patient’s neurocognitive function and quality of life.

## Methods

### Study design

The current study is a prospective cohort study which we have named PASC (post-acute sequel of COVID-19) 24. The study is exploratory in nature as the subject (neurocognitive symptoms after COVID-19 infection) is relatively new. No treatment will be given during the study period. Therefore, the research team has chosen not to perform randomisation nor blinding.

PASC 24 will be assessing and following recruited patients over a period of 24 months (figure 1). Three specific points of evaluation are planned, namely at baseline, after 12 months and 24 months. Recruitment began in 2024, and data collection is currently estimated to be completed by the end of 2026.

**Figure 1 F1:**
[figure not shown]
Flow diagram of recruited patients throughout the study. CSF, cerebrospinal fluid.

### Sample size calculation

The aim is to offer participation in the study to all patients in Örebro County who meet the inclusion criteria. Therefore, the sample size calculation has not been rigorously applied.

However, we have performed calculations based both on previous estimates of the frequency of PASC^10^ and on statistical considerations regarding future analyses. In both cases, we have concluded that a group of approximately 50–100 participants will be possible to recruit and provides space for meaningful analysis. The ethical permission applies to up to 100 participants.

### Study population (sample recruitment)

Participants in the PASC 24 study will principally be recruited primarily from Örebro County but may also be recruited from other areas of Sweden. There are approximately 300 000 inhabitants in Örebro County where the prevalence of SARS-CoV-2 is comparable to other parts of Sweden. A multidisciplinary conference (MDC) will ensure that the referred patients will have hitherto been given adequate and optimal care provision in Örebro County’s primary healthcare system (online supplemental file 1).

The overarching purpose is to detect and describe changes in physical, mental and cognitive function; daily activities and time-to-return to work in patients after experiencing moderate to severe COVID-19 infection. All patients will be living in the community and will be referred through their respective health centres to the MDC at the Department of Rehabilitation at the University Hospital Örebro with several health specialists, including cardiologists, geriatricians, neurologists and general practitioners.

All patients will be prescreened according to their premorbid cognitive and mood status by the PI ([name] specialist in psychiatry and geriatrics), so we can clearly indicate their premorbid status before inclusion in the study. Inclusion will be based on the definition from WHO (post COVID-19 condition (long covid)) concerning post covid syndrome, where the condition is characterised by a range of symptoms which usually start within 3 months of the initial COVID-19 illness and last at least 2 months. We will examine thoroughly patients’ medical records and check for a positive PCR test or positive antibodies in blood tests before inclusion.

Demographic data will be retrieved from medical records as well as in connection with inclusion: gender, age, medical diagnoses, medications, ethnicity, education, employment and degree of sick leave. Basic medical examination will be performed at inclusion: blood pressure, waist circumference, weight, BMI, and smoking habits (table 1).

**Table 1 T1:** Sociodemographic and medical details identified in recruited patients in PASC 24-study

Variable	Variable
Age	Years
Sex	Man/Woman
Language	Swedish/other
Tobacco	Never/Previously/Occasionally/Daily
Social status	Living alone/Living with partner
Occupation	Employed/unemployed/pensioner
Education	Secondary or vocational/Upper secondary/university
Land of birth	Sweden/other
Certified sick-leave	>3 months
Certified sick-leave	Asthma/COPD/cancer/diabetes/heart insufficiency/hypertension/orthostatism/ hypercholesterolaemia/ neurological disorder/hypothyroidism/other
COVID-19 symptoms	Organ/specific symptoms
Smell/taste dysfunction	Remaining symptoms/previously

The *inclusion criteria* include COVID-19 infection confirmed by positive laboratory test (PCR test for SARS-CoV-2) taken during the acute infection, residual neurocognitive symptoms more than 3 months after the initial COVID-19 infection and an age of more than 18 years. Full-spectrum COVID severity cases will be included.

The *exclusion criteria* are severe cancer, dementia and ongoing alcohol or drug abuse. Included participants will then undergo baseline evaluation (figure 1). First when patients are included and have signed the patient consent form, they will then be tested using the neuropsychological tests tested via the digital platform Mindmore AB (www.mindmore.com).^23^ Mindmore is CE marked, approved, and purchased by the Research Centre of Region Örebro County. Trial participants may withdraw from the study at any time. Patients will receive no monetary compensation for study participation.

